**11.Provisions to Monitor the Data to Ensure the Safety of Subjects**

Safety considerations/Patient safety:

Safety monitoring will be undertaken as a part of the clinical trial. A data safety monitoring board will be convened to review safety data on a weekly basis during the conduct of the study.

The major potential side effect will be that of a transfusion reaction that may be manifest with increased fever, hypotension and skin rash. This will be minimized by the ABO and RhD grouping that will be taken for each patient.

An interim review and report to the clinical trial committee will be undertaken when 20 subjects have been recruited

**Definitions**

| **Term** | **Definition** |
| --- | --- |
| **Adverse Event (AE)** | Any untoward medical occurrence in a participant to whom a medicinal product has been administered, including occurrences which are not necessarily caused by or related to that product. |
| **Adverse Reaction (AR)** | An untoward and unintended response in a participant to an investigational medicinal product which is related to any dose administered to that participant.  The phrase "response to an investigational medicinal product" means that a causal relationship between a trial medication and an AE is at least a reasonable possibility, i.e. the relationship cannot be ruled out.  All cases judged by either the reporting medically qualified professional or the Sponsor as having a reasonable suspected causal relationship to the trial medication qualify as adverse reactions. |
| **Serious Adverse Event (SAE)** | A serious adverse event is any untoward medical occurrence that:   - results in death - is life-threatening - requires inpatient hospitalisation or prolongation of existing hospitalisation - results in persistent or significant disability/incapacity - consists of a congenital anomaly or birth defect   Other ‘important medical events’ may also be considered serious if they jeopardise the participant or require an intervention to prevent one of the above consequences.  NOTE: The term "life-threatening" in the definition of "serious" refers to an event in which the participant was at risk of death at the time of the event; it does not refer to an event which hypothetically might have caused death if it were more severe. |
| **Serious Adverse Reaction (SAR)** | An adverse event that is both serious and, in the opinion of the reporting Investigator, believed with reasonable probability to be due to one of the trial treatments, based on the information provided. |
| **Suspected Unexpected Serious Adverse Reaction (SUSAR)** | A serious adverse reaction, the nature and severity of which is not consistent with the information about the medicinal product in question set out:   - in the case of a product with a marketing authorisation, in the summary of product characteristics (SmPC) for that product - in the case of any other investigational medicinal product, in the investigator’s brochure (IB) relating to the trial in question |

Reporting adverse events

Adverse events will be reported in accordance with the local procedures to the REC of NHRA

The following information will be reported: Study name; patient identification, including subject number, initials, sex, age; event (preferably diagnosis); trial drug Reporter Causality Outcome

Determination of causality of an adverse reaction

Probable - Good reason and sufficient documentation to assume a causal relationship.

Possible - A causal relationship is conceivable and cannot be dismissed.

Unlikely - The event is most likely related to aetiology other than the trial product.

Adverse Event reporting period

The AE reporting period for this trial begins as soon as patients have consented to the trial and ends 30 days after the patient’s final study medication visit.

The health status of subjects will be checked at each study visit. The investigator will record all directly observed AEs and all AEs spontaneously reported by the trial subject.

A pre-existing condition is a disorder present prior to the patient entering the trial and does not need to be reported as an AE unless the condition worsens, or episodes increase in frequency during the AE-reporting period. A pre-existing condition will be documented at the screening or baseline study visit.

All adverse events (serious and non-serious) will be recorded by the investigator in patients data collection forms (CRFs) using R&D’s adverse event report form. All adverse events will be recorded by the investigator in patients’ medical records/notes.

All AEs will be followed-up by investigators until the event has resolved or a decision has been taken for no further follow-up.

If a clinically significant abnormal laboratory value occurs, this abnormality will be recorded as an adverse event/reaction.

Reporting serious adverse events

Investigators will notify the sponsor of serious adverse events within 24hrs of becoming aware of the event, together with the REC.

The sponsor will report fatal or life-threatening SUSARs within 5 days and follow-up information within a further 8 days. The investigator will report fatal or life-threatening SUSARs to the IRB within 5 days and follow-up information within a further 8 days by following the request on the Serious Event Initial and Follow-up report forms. The investigator will send all other SUSAR reports to the IRB within a maximum of 15 days.

End of Trial:

The end of the trial will be the date of the last study point of the last patient undergoing the trial.

An end of trial declaration form will be submitted to RCSI Bahrain/ BHF and NHRA REC within 90 days from completion of the trial and within 15 days if the trial is discontinued prematurely. A summary of the trial final report/publication will be submitted to the LREC within 1 year of the end of trial.

Serious adverse events will be reported to the sponsor within 24 hours. All other adverse events will be reported within 5 days.

Potential Benefits to Subjects

Being a part of the study will not guarantee benefits to subject or others. However, possible benefits might be that the subject’s COVID-19 respiratory distress will improve and mitigate the infection within a 1 week period that may lead to the early discontinuation of oxygen administration and prevent the need for ventilatory support. Overall the research may benefit future patients with COVID-19 with severe respiratory distress.

Indemnity/clinical trial insurance

Negligent indemnity will be provided for by the ministry of health and any adverse effects on the patient medical status will be managed by the ministry.

Confidentiality

The study will abide to European GDPR legislation for maintaining confidentiality of data

Ethical permissions

The study will be performed subject to a Local REC favourable opinions from RCSI Bahrain and Salmanyia hospital, and from the National REC NHRA.

Research Governance

This study will be conducted in line with the International Conference for Harmonisation of Good Clinical Practice (ICH GCP) guidelines; the Research Governance Framework for Health and Social Care.

Data handling and record keeping

[name] will act as the data custodian and is responsible for the storage, handling and quality of the study data.

Data will be collected in the case report form to allow for cross referencing to check validity.

Study documents (paper and electronic) will be retained in a secure (kept locked when not in use) location during and after the trial has finished. All essential documents including source documents will be retained for a period of 5 years after study completion (last patient, last study point). A label stating the date after which the documents can be destroyed will be placed on the inside front cover of the case notes of trial participants.

Access to Source Data

Monitoring, audits, and REC review will be permitted and provide direct access to source data and documents. The Lead PI and the researchers assigned by him will have access to the stored data/specimens. Only the Lead PI and the researchers assigned working on this study will be eligible to obtain the data/specimens from the participants during data collection.

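### The serious adverse reaction definition uses a stricter relatedness test and fewer judges than the adverse reaction definition, and the SUSAR definition inherits that test.

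*Protocol*

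**What the plan says.** Three rows of the Definitions table in Protocol section 11 matter here.

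- **Adverse reaction (AR).** The threshold is that "a causal relationship between a trial medication and an AE is at least a reasonable possibility, i.e. the relationship cannot be ruled out". Two parties can make the judgement: "All cases judged by either the reporting medically qualified professional or the Sponsor".
- **Serious adverse reaction (SAR).** The row begins again from an adverse event that is serious and adds its own causal test: in the reporting investigator's opinion, the event must be "believed with reasonable probability to be due to one of the trial treatments". It does not refer back to the AR row.
- **SUSAR.** This is "A serious adverse reaction, the nature and severity of which is not consistent with the information about the medicinal product", so an event must first be a SAR.

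Under the heading on determining causality, the same section gives three grades: *Probable*, *Possible* and *Unlikely*. *Possible* reads "A causal relationship is conceivable and cannot be dismissed". *Probable* is a separate, higher grade that asks for good reason and enough documentation to assume a link. No sentence says which grades make an event related.

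Under the heading on reporting serious adverse events, the investigator notifies every serious adverse event (SAE) to the sponsor and the ethics committee within 24 hours. The 5-day route for fatal or life-threatening cases (with follow-up within a further 8 days) and the 15-day route for the others apply to SUSARs only.

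**The concern.** One would expect a serious adverse reaction to be an adverse reaction that is also serious. Here the SAR row differs from the AR row in two ways: the threshold rises from possibility to probability, and the sponsor's judgement no longer counts. The sponsor's view of relatedness can therefore make a minor event a reaction but cannot do so for a serious one.

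This matters in this population because everyone enrolled has hypoxia and radiological pneumonia. Serious respiratory worsening after plasma has a ready alternative explanation in the disease, so an investigator may well hesitate over causality. The trial is open label and the product is investigational, so a second opinion from the sponsor is a useful check. At stake is whether a suspected, unexpected serious reaction is labelled and reported as one.

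**Working it through.** No arithmetic applies: the point depends on no rate, power or sample-size figure. The check is to read the definitions together.

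**Step 1. Compare the two tests.**

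| | AR | SAR |
|---|---|---|
| Threshold | reasonable possibility; link not excluded | reasonable probability |
| Who may judge | reporting professional or sponsor | reporting investigator |
| Built on the AR row? | – | no; starts from an adverse event |

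**Step 2. Follow the dependence.** A SUSAR must be a SAR, and the 5-day and 15-day routes require a SUSAR. Any event that fails the SAR test therefore fails both routes, even if it meets the AR test.

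**Step 3. Run serious, unexpected events through the definitions as written.**

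| Case | AR | SAE | SAR | SUSAR | 24-hour SAE notice | SUSAR report |
|---|---|---|---|---|---|---|
| Investigator grades *Probable* | yes | yes | yes | yes | yes | yes |
| Investigator grades *Possible* | yes | yes | unclear | unclear | yes | unclear |
| Investigator grades *Unlikely*, sponsor judges related | yes | yes | no | no | yes | no |
| Neither judges related | no | yes | no | no | yes | no |

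The third row follows directly from the wording. The AR row admits the event on the sponsor's judgement ("All cases judged by either the reporting medically qualified professional or the Sponsor as having a reasonable suspected causal relationship"), while the SAR row asks for the investigator's opinion, which is absent.

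The second row needs an inference. The description of *Possible* is close in substance to the AR threshold, and the SAR row's reasonable probability sits more naturally with *Probable*. A site could fairly read the text as excluding *Possible* events from SARs. Because the protocol does not map the grades to the definitions, the entry is unclear rather than no.

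**Step 4. Look for text that reconciles the rows.** None was found. The causality scale, the reporting rules and the safety-monitoring paragraph do not modify the SAR row or say that *Possible* counts as related.

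**The case against.** The strongest reply is that the protocol has a faster safeguard that does not depend on causality. Every SAE reaches the sponsor and the ethics committee within 24 hours, which is sooner than either SUSAR route. The 24-hour rule to the sponsor is stated again after the end-of-trial text. A data safety monitoring board reviews safety data weekly, all adverse events are recorded, and causality is among the items reported. A reader might infer from the definitions that serious harm from plasma would go unreported. The documents do not support that, and this part of the objection stands in full.

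A reader might also infer that an event graded *Possible* can never become a SUSAR. That is too strong as well, since the scale is not tied to the phrase used in the SAR row. Nor can one say what share of events would be affected. The documents give no distribution of causality grades, and events with a strong disease explanation might be graded *Unlikely*, where clarifying that *Possible* counts would change nothing unless the sponsor disagreed.

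Finally, the protocol names no SAR count among its outcomes or analyses, so no planned analysis is shown to be affected.

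These replies narrow the consequence but leave the contradiction. A 24-hour notice says that a serious event happened. It does not identify the event as a suspected unexpected reaction, and it does not trigger the SUSAR report or its follow-up.

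**Conclusion.** The AR and SAR rows set incompatible relatedness tests, and the SUSAR definition inherits the narrower one. For a serious unexpected event judged related only by the sponsor, the loss of SAR and SUSAR status follows from the literal text. For an event graded *Possible*, the loss is a reasonable reading but not a certain one.

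The size is qualitative. What can be lost is the classification, the 5-day and 15-day SUSAR reports, and the follow-up due within a further 8 days. Notification of the event is not lost. No number of affected events can be derived from the protocol. The point does not touch randomisation, the primary outcome, the sample size or the efficacy analysis.

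The conclusion assumes that sites apply the definitions as written and that no separate safety procedure, not referred to in the definitions, overrides them. Definitions and reporting clocks of this kind are protocol content, so the matter is not one left to an analysis plan. It is worth correcting: the defect is real, partly mitigated and cheap to remove.

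**What to change.** Reconcile the rows using the protocol's own AR standard, with two changes in section 11:

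1. Define a SAR as an adverse reaction, as already defined in the table and judged by either the investigator or the sponsor, that meets at least one of the listed seriousness criteria. The SUSAR row then needs no change on this point.
2. Under the heading on determining causality, state that *Probable* and *Possible* both count as related and *Unlikely* does not, and that if the investigator and sponsor differ, either judgement of relatedness is enough.

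The cost is about two sentences of protocol text and, at most, a few more SUSAR reports in a trial of 40 patients, 20 of whom are to receive plasma. The 24-hour SAE rule and the weekly board review stay as they are.

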**12.Dissemination of results and publication policy**

The main findings will be widely reported urgently in the literature as appropriate. It is anticipated that this study will be reported at national and international conferences along with a number of papers in peer reviewed academic journals. The study will be registered at clinicaltrials.gov. Reporting of the study findings will be in accordance with the CONSORT statement (Consolidated Standards of Reporting Trials http://www.consort-statement.org/).

